**Outline of the study protocol**

*Subject eligibility and recruitment*

Data collection is planned between February 2010 and September 2012. Recruitment and final sample size for the analysis should be 32 healthy men, 20-40 years old, who will be recruited at the University of Kiel campus. Since metabolic changes and dysregulation in energy balance is assumed in obese subjects, only healthy and normal weight subjects will be recruited. To assess eligibility of the subjects, they will complete a medical history and physical examination to assess health status. Exclusion criteria for enrollment include

- Smoking
- unstable weight (>2 kg over the past 12 months)
- chronic diseases
- regular use of medications
- family history of type 2 diabetes
- food allergies or special diets (e.g. vegetarian)
- being an athlete.

*Study protocol*

6-week strictly controlled dietary intervention will be carried out at the Institute of Human Nutrition and Food Science at the Christian-Albrechts-University of Kiel. An outline of the study protocol is shown in figure 1. Before the dietary intervention, there is a 1-week pre-intervention period, during which each subject will undergo a hyperinsulinemic euglycemic clamp and an oral glucose tolerance test (OGTT). Prior to the tests, resting energy expenditure (REE) will be measured to determine individual energy requirement during the intervention. Body weight and blood pressure will be measured daily throughout the 6-week dietary intervention.

All subjects will undergo an initial 1-week of overfeeding (OF, +50% of energy requirement), followed by 3-weeks of caloric restriction (CR, -50% of energy requirement) and subsequent 2-weeks of refeeding (RF, +50% of energy requirement). The initial overfeeding period is added to the study protocol to limit minimum body weight. Energy requirement of each subject will be calculated by multiplying resting energy expenditure (REE, measured by indirect calorimetry, Vmax Spectra 29n, SensorMedics®, Viasys Healthcare, Bilthoven, Netherlands) by a sedentary physical activity level of 1.4. Fasting blood samples will be taken at baseline and at the end of each intervention period. An OGTT will be conducted at baseline, as well as after CR and RF. Body weight will be measured daily. Physical activity will be monitored by step counters. Participants will be informed that physical activity should not exceed 5,000 steps a day.

Measurements of REE and OGTT as well as fasting blood sampling will be repeated at the end of caloric restriction and refeeding. Continuous interstitial glucose monitoring, glycemic index testing, and a second euglycemic clamp will be performed at the end of the refeeding period.

[figure not shown]

Figure 1: schematic overview of the study protocol; OGTT, oral glucose tolerance test; CHO, carbohydrate; HGI, high glycaemic index; LGI, low glycaemic index

Participants will arrive at the metabolic ward of the Institute of Human Nutrition and Food Science every morning at 8.30 a.m. after an overnight fast of ≥ 10 h. During the pre-intervention period, they are allowed to leave the institute after all measurements are completed. Throughout the intervention periods, subjects are requested to stay at the institute until dinner.

*Main aim*

Main aim of the study is to determine the impact of glycemic index and glycemic load on insulin sensitivity during a weight cycle in young healthy men. Additionally we would like to assess the effect of carbohydrate intake and glycemic index on resting energy expenditure and substrate oxidation during a strictly controlled diet with caloric restriction and refeeding.

*Secondary aim*

Secondary aim of the study is to determine endocrine determinants of insulin sensitivity and insulin secretion during caloric restriction and refeeding.

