**Methods**

*Diet intervention*

At the end of OF, subjects will be randomized into a normal CHO-intake (50% CHO, 35% fat, 15% protein) and a high CHO-intake group (65% CHO, 20% fat, 15% protein). After CR, both intervention-groups will be further stratified into groups receiving a low glycaemic index (LGI) or a high glycaemic index (HGI) diet: 50%CHO‑LGI, 50%CHO‑HGI, 65%CHO‑LGI and 65%CHO‑HGI (figure 1).

All foods and beverages consumed will be provided during the intervention. Seven-day cycle menus are prepared by an experienced dietitian by using PRODI® software (Nutri-Science GmbH, Freiburg, Germany). GI values of individual foods are taken from published international tables [1]. The GI of the diets is calculated according to WHO/FAO guidelines [2] and averaged 34 units in the LGI and 58 units in the HGI diet, respectively. All diets consist of 50% of total daily energy as carbohydrate, 35% as fat, and 15% as protein. Refeeding diets are not matched for fiber content. Subjects will be instructed to eat all food provided and meal intake will be supervised by a skilled nutritionist. Participants will be allowed to drink water, decaffeinated coffee and tea ad libitum and fluid intake was recorded.

During the initial overfeeding period, subjects will receive a normal mixed-diet. During caloric restriction and LGI vs. HGI refeeding, 50% of the energy intake will be given as a liquid formula diet that is provided free of charge by the InsuLean company: During caloric restriction, the subjects will consume two liquid formula meals per day (InsuLean Vital Protein Creme Royal, InsuLean GmbH & Co. KG, Essen, Germany). During HGI refeeding, two liquid formula meals will be prepared with lactose-free milk (InsuLean Pur, InsuLean GmbH & Co. KG, Essen, Germany) and two servings of grape juice will be enriched with maltodextrin. During LGI refeeding, three liquid formula meals (InsuLean Vital Protein Creme Royal), will be prepared with soy-milk and enriched with lactose and sucrose.

An individual GI of the test meals will be calculated for each participant according to the following equation: glucose iAUC test meal / glucose iAUC OGTT * 100 [3].

The remaining 50% of kilocalories will be provided as HGI and LGI mixed-meals and snacks, respectively. Lower or higher GI versions of key “staple” carbohydrate-rich foods are incorporated into the diet (e.g. lower or higher GI breads, rice, pasta, potato products).

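### Lactose intolerance is not an exclusion criterion, although in refeeding lactose is added to the low-GI formula only

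*Protocol*

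**What the plan says.** **Eligibility** (Protocol, Outline of the study protocol, Subject eligibility and recruitment). The list opens with "Exclusion criteria for enrollment include" and has seven items. The one that concerns food is "food allergies or special diets (e.g. vegetarian". No intolerance or malabsorption criterion appears. For screening, "they will complete a medical history and physical examination to assess health status".

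**Refeeding diets** (Protocol, Methods, Diet intervention). During caloric restriction and refeeding, "50% of the energy intake will be given as a liquid formula diet". In the LGI arm, three formula meals "will be prepared with soy-milk and enriched with lactose and sucrose". In the HGI arm, "two liquid formula meals will be prepared with lactose-free milk" and "two servings of grape juice will be enriched with maltodextrin". On intake, "Subjects will be instructed to eat all food provided", and a nutritionist supervises the meals.

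The LGI and HGI groups are formed only after caloric restriction. The protocol speaks of stratifying at that step and does not say that this second split is random. It gives no amount of lactose and does not mention recording symptoms or handling intolerance.

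**The concern.** Lactose intolerance is not an allergy, and a man who merely drinks little milk is on no special diet, so the list lets him in. What then happens to him depends on his arm: in LGI he is given added lactose in the formula meals daily for two weeks, and in HGI he is not. The eligibility list was not matched to the test diets.

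Random allocation would balance the number of intolerant men in expectation. It would not remove the problem, because the exposure that makes intolerance matter comes after allocation and in one arm only. A difference between LGI and HGI would then carry both the glycaemic index of the diet and the consequences of undigested lactose. The impact of glycaemic index on insulin sensitivity is part of the main aim, and individual GI and CGM glycaemia are the measurements that would show whether the intended GI contrast was achieved.

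**Working it through.** The protocol gives no figure on this point to reproduce. Its 75% power concerns another comparison (step 4). The check is a reading of the text, followed by an illustration of scale.

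**1. Exposure by arm, as stated.**

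| | LGI refeeding | HGI refeeding |
|---|---|---|
| Formula base | soy-milk | lactose-free milk |
| Added sugars | lactose, sucrose | maltodextrin, in grape juice |
| Formula meals | three | two, plus two servings of juice |

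The contrast comes from the lactose added in LGI. The LGI base is soy-milk, so it is not a contrast between ordinary and lactose-free milk. Total lactose per arm is unknown, because the composition of the powders and of the mixed meals is not given.

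**2. Where a direction follows.** Individual GI = glucose iAUC of test meal / glucose iAUC of OGTT × 100. The OGTT uses 75 g glucose, so lactose maldigestion leaves the denominator unchanged. If the test meal is the lactose-enriched formula, undigested lactose lowers the numerator and the ratio falls. CGM glycaemia and absorbed energy move the same way. For clamp M-value or Matsuda-ISI, nothing in the document fixes a sign.

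**3. Scale (every starred input is an assumption).**

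- Refeeding energy with REE 1,750 kcal*: 1,750 × 1.4 × 1.5 = 3,675 kcal a day. The 1.4 and the +50% are in the protocol.
- Formula half: 3,675 × 0.5 = 1,838 kcal.
- Formula carbohydrate, if the formula shares the 50% or 65% of the whole diet*: 1,838 × 0.50 / 4 ≈ 230 g, or 1,838 × 0.65 / 4 ≈ 299 g.
- Lactose at 10 to 30% of that*: about 23 to 90 g a day. Over three meals this is about 8 to 30 g per meal.
- Intolerant men among 16 in LGI* (equal split of 32), at prevalence p*: expected number 16p, and chance of at least one 1 − (1 − p)^16.
- Shift of the LGI mean if each affected man's outcome moved by 20%*, in either direction: p × 20%.

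| p* | Expected men | At least one | Shift of LGI mean |
|---|---|---|---|
| 5% | 0.8 | 56% | 1% |
| 10% | 1.6 | 81% | 2% |
| 20% | 3.2 | 97% | 4% |
| 30% | 4.8 | 99.7% | 6% |

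The third column is the chance that such a man is present, not the chance that a result changes. If the four refeeding groups have 32 / 4 = 8 men each*, the loss of one man is 1/8 = 12.5% of a group.

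**4. The powered comparison.** The sample size rests on Matsuda-ISI after caloric restriction in the 50% and 65% carbohydrate groups, 16 men each. That measurement is taken before the LGI and HGI groups exist, so the added lactose cannot affect it.

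**The case against.** **No contradiction is shown.** The exclusion list is introduced in a way that need not be exhaustive, and a medical history is already required. A man who knows that he is intolerant might be caught there or under special diets. This stands in part. But the history is described as an assessment of health status, and nothing directs a question on intolerance or an exclusion for it.

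**There are safeguards.** Intake is supervised, weight is measured daily, and CGM and individual GI would show an unusually low response. All men also take the powder later used in LGI during caloric restriction, so intolerance to the powder itself could show before the split. This stands too, but supervision controls intake and not absorption, and the lactose enrichment is stated only for LGI refeeding.

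**It is a comparison of whole diets.** The refeeding diets are openly not matched for fibre, and lactose could be seen as one more feature of the LGI diet. That is fair: the issue is attribution to glycaemic index, not selection bias.

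**Stronger readings that the protocol does not support.**

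- A reader might infer that the estimated GI effect on insulin sensitivity is biased in a known direction. Exposure is one-sided, but a sign follows only for glycaemia, individual GI and absorbed energy.
- A reader might infer a mirror-image problem in which fructose intolerance matters only in HGI because of the grape juice. Sucrose in the LGI formula also yields fructose, so that load is not confined to one arm.

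**Conclusion.** The point holds in a limited form. As written, a lactose-intolerant man is eligible, and any malabsorption, symptoms or incomplete intake from the added lactose would occur only if he is in the LGI arm. In such men individual GI, CGM glycaemia and absorbed energy would be lowered for a reason other than the glycaemic index of a digested diet. This weakens the attribution of LGI–HGI differences to glycaemic index.

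The size of any effect on insulin sensitivity cannot be established: the lactose amount, the prevalence and the LGI and HGI group sizes are not stated, and all the figures for scale rest on assumed values. The carbohydrate comparison after caloric restriction, the only one with a power statement, is unaffected. This is a cheap improvement to the GI part of the main aim and does not invalidate the design.

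**What to change.** Add one exclusion criterion: known or suspected lactose intolerance, or intolerance to another component of the study formulas or juices. Apply it to every man before the overfeeding week, so that it cannot depend on the arm, by direct questions in the planned medical history: symptoms after milk, avoidance of milk, symptoms after fruit juice. No diet needs to change.

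The cost is one line and a few questions, a few more screen failures, and a slightly narrower population to which the results apply. The questions would find recognised or symptomatic intolerance. Men who maldigest lactose without noticing would still be enrolled, so the problem would be reduced and not removed.

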**Methods**

*Diet intervention*

At the end of OF, subjects will be randomized into a normal CHO-intake (50% CHO, 35% fat, 15% protein) and a high CHO-intake group (65% CHO, 20% fat, 15% protein). After CR, both intervention-groups will be further stratified into groups receiving a low glycaemic index (LGI) or a high glycaemic index (HGI) diet: 50%CHO‑LGI, 50%CHO‑HGI, 65%CHO‑LGI and 65%CHO‑HGI (figure 1).

All foods and beverages consumed will be provided during the intervention. Seven-day cycle menus are prepared by an experienced dietitian by using PRODI® software (Nutri-Science GmbH, Freiburg, Germany). GI values of individual foods are taken from published international tables [1]. The GI of the diets is calculated according to WHO/FAO guidelines [2] and averaged 34 units in the LGI and 58 units in the HGI diet, respectively. All diets consist of 50% of total daily energy as carbohydrate, 35% as fat, and 15% as protein. Refeeding diets are not matched for fiber content. Subjects will be instructed to eat all food provided and meal intake will be supervised by a skilled nutritionist. Participants will be allowed to drink water, decaffeinated coffee and tea ad libitum and fluid intake was recorded.

During the initial overfeeding period, subjects will receive a normal mixed-diet. During caloric restriction and LGI vs. HGI refeeding, 50% of the energy intake will be given as a liquid formula diet that is provided free of charge by the InsuLean company: During caloric restriction, the subjects will consume two liquid formula meals per day (InsuLean Vital Protein Creme Royal, InsuLean GmbH & Co. KG, Essen, Germany). During HGI refeeding, two liquid formula meals will be prepared with lactose-free milk (InsuLean Pur, InsuLean GmbH & Co. KG, Essen, Germany) and two servings of grape juice will be enriched with maltodextrin. During LGI refeeding, three liquid formula meals (InsuLean Vital Protein Creme Royal), will be prepared with soy-milk and enriched with lactose and sucrose.

An individual GI of the test meals will be calculated for each participant according to the following equation: glucose iAUC test meal / glucose iAUC OGTT * 100 [3].

The remaining 50% of kilocalories will be provided as HGI and LGI mixed-meals and snacks, respectively. Lower or higher GI versions of key “staple” carbohydrate-rich foods are incorporated into the diet (e.g. lower or higher GI breads, rice, pasta, potato products).

*Anthropometric measurements and body composition analysis*

Height will be measured to the nearest 0.1 cm using a stadiometer, with subjects not wearing shoes. Body weight will be measured to the nearest 0.05 kg on an electronic scale (seca 285, seca GmbH & Co KG, Hamburg, Germany) with subjects in underwear and after voiding. Fat mass and fat-free mass will be assessed by Quantitative Magnetic Resonance (QMR, EchoMRI-AH™, Echo Medical Systems, Houston, Texas, USA). Liver fat will be determined by MRI (Magnetom Avanto 1.5-T Siemens, Erlangen, Germany) along with the two-point Dixon method with a volume interpolated breath hold examination.

*Energy expenditure*

Respiratory exchange measurements will be performed by means of an open-circuit indirect calorimeter (ventilated hood system Vmax 29n, SensorMedics®; Sensor Medics 130 GmbH Höchberg, Germany). Oxygen consumption and carbon dioxide production will be continuously measured for ≥ 30 min and REE will be calculated from steady state intervals using a standard formula. Activity energy expenditure (AEE) will be assessed by the SenseWear Pro3 Armband (Body-Media Inc., Pittsburgh, PA) that will be continuously worn on the subjects´ dominant arm.

*Blood sampling and analytical methods*

Fasting blood samples will be collected after an overnight fast (≥10h) at baseline and at the end of each intervention period. Glucose will be measured using glucose oxidase method (BIOSEN C-Line, EKF-diagnostics, Texas, USA). Serum insulin will be determined by electrochemiluminescence immunoassay (Elecsys®, Roche diagnotics, Mannheim, Germany). Leptin, adiponectin, ghrelin and thyroid hormone levels (TSH, fT3, fT4) will measured by radioimmunoassay (RIA 125 Tube Kit, LINCO Research, St Charles, Missouri and Abott Diagnostics, Wiesbaden, Germany). 24-h urinary catecholamine excretion (epinephrine and norepinephrine) will measured by HPLC according to Hollenbach et al, 1998 [4].

*Oral glucose tolerance test*

Participants will undergo a standard OGTT (intake of 75 g glucose) at baseline as well as after CR and RF. Venous blood will be sampled 0, 30, 90 and 120 minutes after glucose intake. Insulin, glucose and ghrelin responses will determined and calculated as incremental AUC (iAUC) and total AUC (tAUC) using the trapezoid rule [5].

*Continuous glucose monitoring*

Subcutaneous interstitial fluid glucose levels will be measured by means of the FreeStyle Navigator® continuous glucose monitoring (CGM) device (Abbott Diabetes Care, Alameda, CA, USA) at the end of the refeeding period. A CGM monitor will be worn for 5 consecutive days, data will be downloaded and glucose profiles will be analyzed. Interstitial glucose iAUC during the day (8.00 -10.00 h), i.e. daytime glycemia, and tAUC during the night (0.00-7.00 h), i.e. nighttime glycemia, will be calculated using the trapezoidal rule [5].

*Hyperinsulinaemic-euglycaemic clamp*

Whole-body IS at baseline and at the end of RF will be assess by the hyperinsulinemic-euglycemic clamp technique according to DeFronzo et al [6]. *M*-value, expressed as mg/kg body weight/min, will be determined during the last 20 min of the hyperinsulinemic glucose clamp as steady state glucose disposal rate calculated from the mean rate of exogenous glucose infusion corrected for glucose space.

*Calculations of fasting and postprandial IS and insulin secretion*

Fasting IS will be assessed using HOMA-index: fasting glucose (mmol/l) x fasting insulin (µU/l) /22.5 [7]. Postprandial IS will be calculated by Matsuda whole-body IS Index (Matsuda-ISI): 10000/(√ (fasting glucose x fasting insulin) x (mean glucose x mean insulin during OGTT)) [8]. 1st-phase insulin secretion will be estimated by Stumvoll-index: 1.283+1.829 x insulin30min – 138.7 x glucose30min + 3.772 x fasting insulin [9]. tAUC-insulin/tAUC-glucose will be estimated to assess overall glucose-stimulated insulin secretion during OGTT [10].

*Statistical analysis*

Cross-sectional analysis between different diet groups will be performed using ANOVA (analysis of variance) after adjustment for co-variables. Longitudinal analysis between caloric restriction and refeeding will be assessed using repeated measures ANOVA. Unpaired t-test indicates that enrollment of 32 subjects (16 each diet group) will provide 75% power for the primary aim of impact of carbohydrate intake on insulin sensitivity with a 15% higher Matsuda-ISI after CR in the 50%CHO diet group compared to the 65%CHO diet group. Differences were considered significant if p ≤ 0.05.

2. Carbohydrates in human nutrition. Report of a Joint FAO/WHO Expert Consultation. (1998). FAO Food Nutr Pap 66: 1–140..

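### The CGM measure of daytime glycemia is defined over 8.00 to 10.00 h, a two-hour morning window that contradicts its own label

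*Protocol*

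**What the plan says.** The Methods section, under Continuous glucose monitoring, defines two summaries of the interstitial glucose profile. The first is "Interstitial glucose iAUC during the day (8.00 -10.00 h), i.e. daytime glycemia". The second is the "tAUC during the night (0.00-7.00 h), i.e. nighttime glycemia, will be calculated using the trapezoidal rule". On wear time it says: "A CGM monitor will be worn for 5 consecutive days, data will be downloaded and glucose profiles will be analyzed". No other daytime window appears anywhere in the protocol.

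The Study protocol section gives the daily routine. Participants come to the ward "every morning at 8.30 a.m. after an overnight fast of ≥ 10 h", and "Throughout the intervention periods, subjects are requested to stay at the institute until dinner". It also sets what happens in the same part of the trial as the CGM: "Continuous interstitial glucose monitoring, glycemic index testing, and a second euglycemic clamp will be performed at the end of the refeeding period", and "Measurements of REE and OGTT as well as fasting blood sampling will be repeated at the end of caloric restriction and refeeding".

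Under Diet intervention, the contrast between the refeeding diets is spread over several eating occasions a day. Half the energy comes from formula: two meals plus two servings of enriched grape juice in the high-index arm, three meals in the low-index arm. The other half comes from mixed meals and snacks.

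**The concern.** The outcome is labelled as glycemia during the day, but the printed clock times cover only a short stretch of the morning. Part of that stretch falls before the participant has arrived, still fasted. An analyst who follows the text would compute an incremental area over a fasting interval plus part of the response to one meal, and would report it as daytime glycemia. A real difference between the refeeding diets that builds up over lunch, snacks and dinner would not be seen. An analyst who quietly used a longer window would depart from the protocol. Either way the reported outcome and its written definition would not match.

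**Working it through.** The check is clock arithmetic on the printed times.

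**Inputs**
- Day window 8.00 to 10.00 h and night window 0.00 to 7.00 h (Continuous glucose monitoring).
- Fasted arrival at 8.30 a.m. and stay until dinner (Study protocol).
- Resting energy expenditure measured for at least 30 minutes (Energy expenditure).

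**Which clock.** The night window writes midnight as 0.00, which is 24-hour notation. Read the same way, 10.00 h is ten in the morning.

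**Length and coverage as printed**
- Day window: 10 − 8 = 2 h. Night window: 7 − 0 = 7 h.
- Share of the full day: 2/24 = 8.3%.
- Share of the hours outside the night window: 2/(24 − 7) = 2/17 = 11.8%.
- Hours in neither window: 24 − 2 − 7 = 15 h.

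**What the two hours can contain**
- Before the fasted arrival: 8.30 − 8.00 = 30 min, and 30/120 = 25% of the window.
- Left after arrival: 120 − 30 = at most 90 min.
- Left on a day when resting energy expenditure is measured first: 90 − 30 = at most 60 min.

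Even a meal eaten immediately on arrival would be followed for at most 90 minutes, less than the 120 minutes over which the protocol follows glucose after the OGTT load. Meal times are not stated. On ordinary timing, only the first meal can start inside the window.

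**If 10 p.m. was meant (assumption)**
- Day window: 22 − 8 = 14 h, which is 14/2 = 7 times the printed length.
- Hours in neither window: 24 − 14 − 7 = 3 h.

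The 14-hour reading fits the label, the stay until dinner and the 7-hour night window. The printed reading fits none of them.

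**The case against.** The strongest reply is that this is a slip of clock notation and not a design choice. The protocol writes the arrival time with a.m., so its notation is mixed, and 10.00 may well stand for ten in the evening. If the analysts use that window, lunch and dinner are not lost. This stands as the likeliest explanation, but it does not remove the point. The text is the definition of an outcome, it is wrong by a factor of seven on that reading, and nothing else in the protocol gives the intended time.

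Several stronger readings are tempting, and the protocol does not support them.

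- *CGM is the only measure of the glycemic effect of the diets.* It is not. Under Diet intervention, an individual glycemic index of the test meals is calculated for each participant, and the CGM also yields the night measure.
- *The OGTT, clamp or glycemic index tests contaminate the window.* They are placed at the end of refeeding, as the CGM is, and an OGTT started at 8.30 would run 120 minutes to 10.30 and fill the rest of the printed window. But no test clock times or CGM dates are given, and the schedule figure is not available here. Overlap is possible but not shown, and the number of affected mornings cannot be counted.
- *The tests would create a false difference between diets.* Every participant has the OGTT and the clamp, and the clamp holds glucose at a normal level. No mechanism for a spurious difference follows from the text.
- *The iAUC baseline and the handling of test days are missing.* Both are details that a statistical analysis plan commonly settles, so their absence here is no finding.
- *The trial's main result is at risk.* CGM glycemia is named in neither the main nor the secondary aim, and the power statement rests on Matsuda-ISI after caloric restriction, before the CGM takes place.

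**Conclusion.** The daytime window is wrong as written. It covers 2 of 17 non-night hours (12%), at least a quarter of it is fasting, and it cannot represent glycemia over the fed day. The length and the fasting share follow directly from the printed times. The statement that lunch, later snacks and dinner fall outside assumes ordinary meal timing, which the fasted 8.30 a.m. arrival and the stay until dinner make reasonable. That 22.00 h was intended is probable but unconfirmed. The consequence is confined to the CGM daytime outcome. Randomisation, sample size and the Matsuda-ISI comparison do not depend on it.

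**What to change.** State the daytime window on one 24-hour clock so that it spans the whole fed day, probably 8.00 to 22.00 h, with the sponsor confirming the intended end time before the CGM data are analysed. This costs one corrected clock time and no extra data, because the monitor is worn for 5 consecutive days in any case.

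If the schedule shows that an OGTT, clamp or glycemic index test falls within those 5 days, the affected hours can be left out of daytime glycemia at the cost of a few CGM hours. If there is no overlap, nothing further is needed.

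### The Matsuda, Stumvoll and HOMA formulas cannot safely be followed as printed: root scope, constant, units and one label need verification before analysis

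*Protocol*

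**What the plan says.** All three formulas stand in the protocol's Methods, in the paragraph on calculating fasting and postprandial insulin sensitivity and insulin secretion.

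- **Matsuda-ISI:** "10000/(√ (fasting glucose x fasting insulin) x (mean glucose x mean insulin during OGTT", followed by two closing brackets. No units are given.
- **Stumvoll index:** "1st-phase insulin secretion will be estimated by Stumvoll-index", with the formula "1.283+1.829 x insulin30min – 138.7 x glucose30min + 3.772 x fasting insulin". No units are given.
- **HOMA:** presented as the measure of fasting insulin sensitivity, with the formula "fasting glucose (mmol/l) x fasting insulin (µU/l) /22.5". These are the only glucose and insulin units in the paragraph.

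The Statistical analysis paragraph states that "enrollment of 32 subjects (16 each diet group) will provide 75% power" for a 15% higher Matsuda-ISI after caloric restriction in the 50% carbohydrate group. Clamps are done only at baseline and at the end of refeeding. Insulin secretion belongs to the secondary aim.

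**The concern.** These are operative endpoint definitions written into the protocol, not details left to an analysis plan. Someone who programs them as printed meets three problems.

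1. In the Matsuda line, the bracket after the root sign closes after fasting insulin. The fasting terms then enter to the power 0.5 and the OGTT means to the power 1.
2. In the Stumvoll line, the constant is too small to offset the glucose term, so a secretion estimate can come out negative.
3. HOMA is a product of glucose and insulin, so it rises as sensitivity falls. It carries the same insulin sensitivity label as Matsuda-ISI, which moves the other way. The title of the protocol's own reference 7 speaks of insulin resistance.

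The Matsuda line matters most. The powered comparison is made after caloric restriction, when no clamp is done, so insulin sensitivity at that point rests on the fasting and OGTT formulas alone.

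**Working it through.** All glucose, insulin and SD values below are assumptions, because the protocol prints none.

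**Stated power.** The 75% cannot be reproduced without an SD. With 16 per group and a two-sided t-test at 0.05, 75% power needs a standardised difference of 0.9625, so the implied CV is 15/0.9625 = 15.6%. One-sided, it is 15/0.839 = 17.9%. At CVs of 15%, 20% and 30% the two-sided power would be 78%, 54% and 28%.

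**Matsuda-ISI.** Let F be the fasting product and M the product of the OGTT means. The literal reading is 10000/(√F x M); the full root is 10000/√(F x M).

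- *Level.* With glucose 85 (fasting) and 115 mg/dl (OGTT mean) and insulin 6 and 45 µU/ml, the literal reading gives 0.086 and the full root 6.16.
- *Units.* Over three insulin pairs (4/25, 6/45, 10/70 µU/ml), the full root in mg/dl gives 3.8 to 10.1. The literal reading in mmol/l (4.7 and 6.4), the paragraph's only glucose unit, gives 3.3 to 14.4. These ranges overlap, so the size of the values would not reveal which version had been computed.
- *Order.* Keep glucose at 85 and 115 mg/dl. Subject A has insulin 4 fasting and 60 mean; subject B has 9 and 30.
  - Literal: A = 10000/(√340 x 6900) = 0.079; B = 10000/(√765 x 3450) = 0.105.
  - Full root: A = 10000/√(340 x 6900) = 6.53; B = 10000/√(765 x 3450) = 6.16.
  - The order reverses, so this is not a rescaling.
- *Effect.* A ratio of 1.15 under the full root becomes, under the literal reading, 1.15 if it arises in F only, 1.15^1.5 = 1.233 if split equally, and 1.15² = 1.3225 if in M only.
- *Power.* A simulation used 20,000 trials per setting, log-normal components, log-SD 0.158 for the full-root index and F–M correlations of 0.3, 0.6 and 0.9. Full-root power was 67–68%. Under the literal reading it was 34–37% with the effect in F, 64–66% if split, and 87–89% in M. The 67–68% is a comparator, not a reproduction of the 75%: ln(1.15)/0.158 = 0.885, below the 0.9625 needed.

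**Stumvoll index.** The protocol uses the comma for thousands ("physical activity should not exceed 5,000 steps a day") and the dot for decimals, so the constant reads as one point two eight three.

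- *pmol/l and mmol/l.* With insulin 350 at 30 minutes and 40 fasting, the insulin terms are 1.829 x 350 + 3.772 x 40 = 791.0. At glucose 7 the index is 1.283 + 791.0 − 970.9 = −179; at glucose 9 it is 1.283 + 791.0 − 1248.3 = −456. With 1283 as constant the results are +1103 and +826.
- *Break-even.* With fasting insulin 40, the index is zero at insulin30 = (138.7 x glucose − 1.283 − 150.88)/1.829. That is 410 pmol/l at glucose 6.5 and 561 at 8.5. At 500 (glucose 7, fasting 50) and 600 (glucose 7.5, fasting 60) it is positive: +134 and +285.
- *µU/ml.* With insulin 50 and 6 and glucose 7.5: 1.283 + 91.45 − 1040.25 + 22.63 = −925.
- *µU/l, the printed unit.* With insulin 50,000 and 6,000 and glucose 8, the insulin terms are 91,450 + 22,632 = 114,082 and the glucose term is 1,110, or 0.97% of them.

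**HOMA.** At 5 mmol/l and 6.7 µU/ml: 5 x 6.7/22.5 = 1.49. In the printed unit insulin is 6,700 µU/l, and the result is 1,489.

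**The case against.** **The root.** A root bar over both products could have been lost when the PDF was converted to text, leaving exactly this string. A reader might infer that the protocol's Matsuda formula is proven wrong. The documents do not show that: the full-root form rests on reference 8, which is not at hand. What stands is that the formula as available is literally a partial root, has no units, and is not settled by any second statement.

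**Negative secretion.** A reader might infer that the printed Stumvoll index is always negative. It is not: it turns positive at high 30-minute insulin, and in µU/l it is about +113,000. The µU/l case is no rescue, because glucose then has almost no weight. That 1283 and pmol/l are intended is likewise an inference to be checked against reference 9.

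**Group comparisons.** A wrong additive constant cancels in raw differences between arms and over time, and a uniform factor of 1000 leaves HOMA tests unchanged. The protocol plans ANOVA and repeated measures ANOVA and states no log or percentage-change analysis of these indices. This stands, and limits the harm from the constant and the HOMA unit. It does not cover the Matsuda root or the Stumvoll insulin unit, both of which change relative weights.

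**Sample size.** A reader might infer that the 75% power is invalid. Nothing shows which formula lay behind it, no SD is printed, and the simulated power moves in either direction.

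**Citation.** Each index is named and referenced, so an analyst may well use the published form. That lowers the risk without removing it.

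**Conclusion.** The concern holds in a limited form: the three formulas cannot safely be followed as printed.

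- **Matsuda-ISI** is ambiguous and unitless. The choice of reading can reverse subjects and turn a 15% effect into anything from 15% to 32%.
- **Stumvoll** has a constant that gives negative secretion over a wide range of assumed ordinary values, and it lacks the units that fix the weight of glucose against insulin. The constant alone affects levels, signs and percentage changes, not raw arm differences.
- **HOMA** has a label opposite to its direction and an insulin unit that appears 1000-fold off; the unit affects levels only.

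The sizes depend on the assumed glucose and insulin values. The intended forms remain apparent rather than proven until the references are checked. Whether 32 subjects suffice is left open.

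**What to change.** Before analysis, check the three formulas against the protocol's references 7 to 9 and amend the paragraph:

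1. Bracket the Matsuda root explicitly (apparently over all four terms) and state the glucose and insulin units.
2. Correct the Stumvoll constant (apparently 1283) and state its insulin and glucose units.
3. Correct the HOMA insulin unit (apparently µU/ml) and label the index insulin resistance.
4. Confirm that the 15% effect and 75% power refer to the verified Matsuda-ISI.

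One worked example per index would guard against a repeat. The cost is a few lines of text, with no change to data or design.
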